### Intervention

Patients assigned by randomization to ARM1 (experimental arm) receive letrozole 2.5 mg (Femara®, Novartis) and patients assigned to ARM2 (control arm) will receive placebo (Novartis). The start is within 14 days after randomization from initial visit (M0), and orally taken once daily for a maximal total duration of 5 years or until symptomatic relapse, or other discontinuation reasons.

The tablet can be taken with or without food and should be swallowed whole with a glass of water or another liquid.

Letrozole or Placebo will be dispensed by the study nurse to the patient during her consultation at the center. The patient will receive 3-monthly supply of the experimental drug (after 2 years. 6-monthly supply). The study visits are scheduled according to the usual routine visits during the active study period.

### Objectives

The primary objective in this study is to evaluate the effect of letrozole maintenance therapy after standard surgical and chemotherapy treatment on PFS compared to placebo in patients with newly diagnosed ER positive epithelial ovarian cancer (histologic subtype: serous or endometrioid of low/high grade, including fallopian tube and primary peritoneal cancer). At FIGO Stage II-IV, with or without residual disease and with or without concomitant anti-VEGF and/or PARPi medication, whose cancer has not progressed by the end of adjuvant chemotherapy treatment.

The secondary objectives are to evaluate the letrozole maintenance treatment compared to placebo in terms of.Overall Survival (OS)Quality-Adjusted Progression Free Survival (QAPFS)Time to First Subsequent Treatment (TFST)Quality-adjusted Time Without Symptoms of disease and Toxicity (Q-TWiST)Health Related Quality of Life (QoL) assessed by EQ-5D-5L, FACT-ES and FACT-O (Fig. 2)

**Fig. 2 Fig2:**
[figure not shown]
Overview of all time-dependent endpoints. *QAPFS   *Quality-adjusted Progression Free Survival, *Q-TWiST   *Quality-adjusted Time Without Symptoms and Toxicity,* TOX*   Toxicity*, TWIST*   Time Without Symptoms and Toxicity*, REL*  Relapse*, PFS   *Progression Free Survival*, OS   *Overall Survival

Additionally, the following explorative and translational objectives are evaluated:To explore the correlation between the activity values of the wearable activity tracker (objective QoL measuring tool) and the patient reported QoL scoresTo explore the feasibility of digitally obtained biomarkers for clinical trialsTo explore the efficacy of letrozole maintenance therapy in correlation to anti-VEGF and PARPi maintenance therapy as measured by PFSTo explore the efficacy of letrozole maintenance therapy in comparison to no maintenance therapy (placebo) according to presence/absence of residual tumor tissue as measured by PFSTo explore the effect of resilience (Connor-Davidson Resilience Scale 10 score categories) on PFS and over timeTo explore the resectability in primary or interval debulking surgery in correlation to the Age Adjusted Charlson Comorbidity Index (AACCI) and the G8 fragility questionnaire scoreTo assess the safety and tolerability of the letrozole group in comparison to the placebo control group and historic breast cancer cohortTo determine molecular markers of ER + /ER- and its association with clinico-pathological parameters [35–38]To determine pathways involved in estrogen response (e.g. EIG121, ESR1/2 and PI3KCA) [39–41]To determine the mutational load of involved tumorsTo determine the predictive role of a glycomic signature in association with clinico-pathological parameters [42]To determine synergistic effects of combined maintenance therapies by state-of-the-art molecular methods [43, 44]

### Sample size consideration and statistical analyses

#### Sample size considerations of the whole cohort

We estimated how many events are needed to achieve a 90% power to detect a hazard ratio (HR) of 0.70 between the two treatment arms (hazard letrozole/hazard placebo, assuming an exponential distribution of PFS). From the ICON7 adjuvant trial [10], which investigated bevacizumab in the adjuvant maintenance setting, it is expected that PFS is approximately exponentially distributed and the median PFS under standard care is 18 months. The assumed HR of 0.70 would increase the median PFS in the treatment arm to 25.7 months.

Calculations were done assuming a two-sided alpha level of 5% and a log-rank test for comparison. The approximation described by Machin et al., (2009) resulted in a required sample size of 330 events, i.e., cases with progression over both study arms [45]. The recruitment will continue until this number of events is observed and the power of 90% has been achieved. When assuming, in addition to the aforementioned conditions, a uniform recruitment rate during three and a half years and a dropout rate of 10%, a total number of 540 patients would suffice to achieve the target number of 330 events five years after study start (calculated using the method by Lachin & Foulkes, 1986) [46].

#### Sample size considerations specific for the low grade cohort, LOGOS

Assumptions about efficacy for the power calculations are based on the retrospective analysis of Gershenson et al*.* [17]. We assume exponential PFS distributions, the analysis by a two-sided log-rank test with alpha level 0.05, and a power of 80%. With an accrual duration of 7 years and a follow-up phase of 5 years after accrual of the last patient, a dropout rate of 15%, and a median PFS of 36 months in the control arm and 60 months in the experimental arm (i.e. a hazard ratio of 0.6 between arms). Because the main protocol of the MATAO trial schedules its final PFS analysis at approximately 5 years after inclusion of the last MATAO patient (while recruitment into the LOGOS stratum will still be ongoing) and states grade as a factor for subgrouping, technically, this constitutes an interim analysis of the LOGOS data. To account for this interim analysis, we plan an O’Brien-Fleming group sequential design with one interim look and one final look. The sample size / power calculations were performed using ADDPLAN version 6.1. Accounting for 15% dropout, 186 patients (i.e. approximately 2.2 patients per month) should be recruited into LOGOS in order to have the 158 evaluable patients, necessary to achieve a power of 80% with this O’Brien-Fleming group sequential design. The boundaries for the group sequential design at the interim look will be based on the actual number of observed events and will be calculated using the alpha-spending function for an O’Brien-Fleming design. The final analysis will be performed after observation of 121 events.

### Statistical analyses

Patients will be analyzed according to the intention-to-treat principle, i.e. all patients will be analyzed according to the treatment group they were allocated to, regardless of adherence.

### Primary analysis

A Cox proportional hazards regression model will be implemented to study whether treatment influences PFS. In this model, we will stratify by grade of cell differentiation (HGOC or LGOC). The proportional hazards assumption will be checked by inspecting the scaled Schoenfeld residuals and formally tested by performing the Grambsch-Therneau test. No matter whether a violation of proportional hazards is detected, the hazard ratio (HR) with its 95% confidence interval will be presented as well as the p-value for that HR. If there is an indication of a non-proportional hazard rates, the restricted mean survival time (and its difference between arms) at t* = 5 years, and its confidence interval will be reported since they provide a more insightful statistic in such cases (following the recommendations of Royston and Mahesh [47]) Furthermore, Kaplan–Meier curves will be plotted by treatment arm.

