## Background

The prognosis of patients with ovarian cancer is still poor with a 5-year relapse rate of 75% for advanced high grade serous and endometrioid ovarian cancers (HGOC) [1–3]. However, better treatment options including maximal cytoreductive surgical efforts and new targeted-therapies has improved the outcome of particularly HGOC over the last decade. Several drugs have been evaluated in clinical trials in the primary and recurrent setting. The most promising medical strategies to delay progression of ovarian cancer after primary surgical and adjuvant treatment as of today are (a) PARP-inhibition with olaparib [4, 5], niraparib [1], rucaparib [6, 7] and others or (b) inhibition of angiogenesis with targeting agents like bevacizumab [8–10], pazopanib [11], cediranib [12, 13], trebananib [14] and others. Bevacizumab, a vascular endothelial growth factor (VEGF)-antibody is approved for maintenance treatment based on a post-hoc analysis for high-risk cancers [15]. Olaparib, a PARP-inhibitor, is approved for high-grade serous ovarian cancer in the recurrent setting after re-introduction of platinum-based chemotherapy [15]. Additionally, Olaparib showed tremendous benefit in BRCA mutated patients in the first adjuvant SOLO-1 maintenance trial [4]

Recently, the results of three separately conducted clinical trials with various PARP inhibitors and different combination treatments, PRIMA, PAOLA, and, by Coleman et al*.,* 2019, VELIA, demonstrated substantial benefit when incorporating PARPi upfront in the treatment of newly diagnosed ovarian cancer, leading to a meaningful increase of progression-free survival [1, 5, 16]. However, with a substantial treatment discontinuation (12%-54%), dose reduction (28%-70.9%), and dose interruption (20%-79.5) due to adverse events [1, 4, 5], and with a note that, the impact of improved surgical resection techniques could not be ignored as residual disease, after upfront surgery, is still the best prognostic indicator for relapse [3].

Despite all these new treatment options and the subsequent increase on progression-free survival (PFS) for distinct groups of ovarian cancer patients, the overall survival (OS) remains poor with a high relapse rate [1, 2, 4]. This underlines the need for the exploration of treatment options that will increase PFS and OS without decreasing quality of life (QoL).

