### Inclusion criteria

Patients must be ≥ 18 years of ageWilling and able to attend the visits and to understand all study-related proceduresPrimary, newly diagnosed FIGO Stage II to IV and histologically confirmed low or high grade serous or endometrioid epithelial ovarian/fallopian tube/peritoneal cancer(Interval-) debulking performedEastern Cooperative Oncology Group (ECOG)-Performance Status 0–2Signed informed consents (ICF-1; ICF-2)Paraffin-embedded tissue or paraffin-embedded cell block (from ascites) availablePositivity (≥ 1%) for ER expression (as determined by the central Histopathology Core Facility of the MATAO trial)At least 4 cycles of platinum-based chemotherapy (neoadjuvant allowed)Negative serum pregnancy test in women of childbearing potential (women of childbearing potential defined as: premenopausal or less than 12 months of postmenopausal amenorrhea, and who have not undergone surgical or radiation sterilization)

Note: Patients under concurrent maintenance treatment with Bevacizumab and/or PARP Inhibitors are eligible

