### Randomization

After written informed consent has been obtained and all eligibility information has been entered into the system and all eligibility criteria are met, the secuTrial® database will provide the study site with a unique, anonymous patient identifier (randomization number). Subjects will be assigned 1:1 to letrozole or placebo. Randomization is performed from the secuTrial® system by stratifying the grade of cell differentiation (low or high) using the variance minimization procedure. After full completion of a subject’s enrollment the secuTrial® system creates automatically a confirmation of the successful randomization process, sent via Email blinded to the individual site and the coordinating office, and unblinded to the Clinical Manufacturing Organization (CMO). 

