### Subgroup analysis

We will explore the impact of the experimental treatment vs the control in the following subgroups:- Bevacizumab treatment.- PARP inhibitor treatment.- Residual disease.- Grade (LGOC/HGOC).- Weak and strong ER expression.- Resilience categories/scores.- The elderly population (≥ 75 years).

For each subgroup, the primary analysis will be repeated. No other subgroups or subgroup analyses are pre-specified.

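### The primary Cox model uses grade alone and leaves out residual disease and FIGO stage, both fixed before randomisation: a missed gain in precision, not an error

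*Protocol article*

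**What the plan says.** All references are to the protocol article.

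- **Primary analysis:** a Cox model for PFS, with "In this model, we will stratify by grade of cell differentiation (HGOC or LGOC". No further covariate is named. Secondary analysis repeats that grade is the stratum used for the primary endpoint.
- **Randomization:** "Subjects will be assigned 1:1 to letrozole or placebo", carried out "by stratifying the grade of cell differentiation (low or high) using the variance minimization procedure". Grade is therefore the only factor in both the allocation and the analysis.
- **Background:** "residual disease, after upfront surgery, is still the best prognostic indicator for relapse". The same section credits first-line PARP inhibition with a substantial PFS benefit.
- **Inclusion criteria:** FIGO stages II to IV are admitted, debulking must already have been done, and "Patients under concurrent maintenance treatment with Bevacizumab and/or PARP Inhibitors are eligible".
- **Subgroup analysis:** the list includes "Bevacizumab treatment.- PARP inhibitor treatment.- Residual disease". Stage is not on it.
- **Sample size considerations of the whole cohort:** the target is to "achieve a 90% power to detect a hazard ratio (HR) of 0.70 between the two treatment arms", and "Calculations were done assuming a two-sided alpha level of 5% and a log-rank test for comparison".

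**The concern.** The authors name residual disease as the strongest predictor of relapse and admit patients both with and without it, across three FIGO stages. They then use neither variable in the allocation or in the primary model. Repeating the primary analysis within a residual-disease subgroup does not recover the lost information.

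Two things are at stake. In a Cox model, omitting a strong prognostic factor pulls the estimated treatment hazard ratio towards 1 relative to the effect among comparable patients, and costs power at a fixed number of events. Also, a chance difference between arms in an omitted factor passes straight into the estimate, and correcting for it after unblinding invites dispute.

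**Working it through.** **1. The plan's own figure.** Inputs: HR 0.70, two-sided alpha 5%, power 90%, log-rank test (Sample size considerations of the whole cohort); 1:1 allocation (Randomization).

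- Events (Schoenfeld) = 4(z₀.₉₇₅ + z₀.₉₀)² / (ln 0.70)² = 4 × 10.507 / 0.12722 = 330.4, so 331 against the stated 330.
- Power at 330 events = Φ(√330 × 0.3567/2 − 1.960) = Φ(1.280) = 0.8997.
- Experimental median = 18/0.70 = 25.7 months, as stated.
- The Freedman formula gives 338 events, and 89.4% power at 330.

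The stated figure reproduces.

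**2. Which factors are baseline.** Debulking and FIGO stage are eligibility items, so residual disease and stage precede randomisation. For PARP inhibitor and bevacizumab, the article says only that patients on concurrent treatment are eligible. It does not say that this treatment must have been started or decided by randomisation.

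**3. Power at 330 events.** The article gives no prevalence or prognostic HR for these factors, so all of the following are assumptions:

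- 540 patients, uniform accrual over 42 months, analysis at the 330th event, 10% dropout over 60 months, 3,000 simulated trials per scenario.
- Residual disease 35%, higher stage 30%, PARP inhibitor 35%, bevacizumab 45%, all independent.
- Low grade 10%, with HR 0.5.
- Baseline hazard set so that the control median is 18 months.

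Prognostic HRs, in the order residual disease / stage / PARP inhibitor / bevacizumab:

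- weak: 1.25/1.2/0.85/0.9
- moderate: 1.5/1.3/0.7/0.85
- strong: 2.0/1.5/0.5/0.8
- very strong: 2.5/1.7/0.4/0.7

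Reading A takes 0.70 as the HR that the grade-only model estimates. Reading B takes 0.70 as the HR conditional on the covariates.

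| Factors | Reading | Grade-only HR | Grade-only power | + residual disease, stage | + all four |
|---|---|---|---|---|---|
| Weak | A | 0.700 | 90.5% | 91.0% | 90.8% |
| Weak | B | 0.703 | 89.3% | 90.2% | 90.1% |
| Moderate | A | 0.700 | 90.7% | 92.0% | 92.5% |
| Moderate | B | 0.710 | 88.3% | 89.3% | 89.9% |
| Strong | A | 0.700 | 90.3% | 93.0% | 95.0% |
| Strong | B | 0.727 | 82.9% | 86.6% | 89.4% |
| Very strong | A | 0.700 | 90.0% | 94.2% | 97.1% |
| Very strong | B | 0.743 | 77.3% | 83.7% | 89.4% |

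Gains in points, computed before rounding (lower to higher reading):

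- Residual disease and stage: 0.5–0.9, 1.0–1.3, 2.7–3.7, 4.3–6.4.
- All four: 0.4–0.8, 1.6–1.8, 4.6–6.5, 7.1–12.0.

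The Monte Carlo standard error of a gain is 0.3 to 0.7 points, so the smallest gains are barely distinguishable from zero. In a separate simulation with no prognostic effect (1,500 trials), power was 90% unadjusted and 89% adjusted, with Monte Carlo error about 1 point. That shows no detectable cost.

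**4. Chance imbalance.** Assume 35% residual disease and 270 patients per arm.

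- SD of the between-arm difference = √(2 × 0.35 × 0.65/270) = 0.041, so 1.96 × 0.041 = ±8 percentage points is within ordinary chance.
- If residual disease carries HR 2.0, the log-HR moves to first order by 0.08 × ln 2 = 0.055. An HR of 0.70 would then read as about 0.66 to 0.74 without adjustment.

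**The case against.** The strongest reply is that this is a preference about efficiency. The analysis mirrors the randomisation, its type I error does not depend on covariate adjustment, and chance imbalance in a randomised trial is not bias. All of that is right, and it is why the point is not an error. It does not remove the point: the article fixes the model here rather than deferring it, and it singles out the omitted variable as the leading predictor of relapse.

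A reader might infer that the trial falls short of its 90% power. The documents do not support that. The sample-size section sets 0.70 between the arms and ties it to whole-cohort medians of 18 and 25.7 months. That is reading A, under which the grade-only model keeps its planned power and adjustment is a bonus. A shortfall appears only under reading B.

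A reader might also take PARP-inhibitor and bevacizumab use to be known at randomisation. The article does not establish this, and adjusting for use begun later would condition on a post-randomisation variable.

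Two limits of the simulation also stand. The factors were taken as independent, although the Discussion links bevacizumab to stage III–IV, and PARP inhibition to high grade, BRCA mutation and response. Every prognostic HR is assumed.

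**Conclusion.** The point holds as a missed gain in precision and in robustness to chance imbalance. The planned analysis is valid. For the two factors that are clearly baseline, the gain is about 0.5 to 4 points for weak to strong prognostic effects and up to about 6 for very strong ones. With all four it is about 0.4 to 7 points, reaching about 12 only if the factors are very strong and 0.70 is a conditional HR. A loss of several points cannot be stated as fact: with weak to moderate factors the gain is under 2 points. The direction follows from the model; the size rests on the assumed prevalences and HRs. The change is worth making because it costs little, not because the present plan fails.

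**What to change.** Before unblinding, amend the primary analysis so that the grade-stratified Cox model includes residual disease (yes/no) and FIGO stage as fixed covariates, with the stage categories defined in advance. Add PARP inhibitor and bevacizumab only as started or planned at randomisation, and only if that status is documented; never include use begun later. Report the grade-only HR beside the adjusted one as a sensitivity analysis.

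The cost is a change of wording. Residual disease is already needed for a listed subgroup and stage for eligibility, so neither calls for new data. For PARP inhibitor and bevacizumab, someone must first check that status at randomisation was captured. The small downside is that the adjusted HR is conditional on the covariates and need not equal the grade-only HR, which is why both should be shown.

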### Secondary analysis

The effects of the letrozole treatment on the secondary endpoints OS and TFST are tested applying the same analysis as described for the primary endpoint. The treatment’s effects on QoL, QAPFS and Q-TWiST are analyzed in a linear regression where baseline QoL is included as a covariate and the same stratum that was included for the primary analysis, i.e. grade of cell differentiation, is included as random effect. The sample size required for achieving the primary objective (assessing survival difference) will very likely suffice for a good estimate of the treatment arm difference for these continuous QoL outcomes. QAPFS, and Q-TWiST are based upon QoL assed using EQ-5D-5L and will be reported for each arm. In addition, descriptive statistics will be shown for all listed variables, broken down by study arm. The precise development of QoL over time will be presented graphically based on both the mean/median scores as well as on the proportion of patients reaching MICD, as will be described in detail in the subsequent statistical analysis plan. Similarly, the severity of side-effects of treatment over time will be shown (Fig. 3).

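### The RMST difference is promised only after a non-proportionality screen that misses moderate departures more often than not; report it in all cases, at a horizon that follow-up supports

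*Protocol article*

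**What the plan says.** The Primary analysis section specifies a Cox model for PFS, stratified by grade. Proportional hazards are checked by looking at scaled Schoenfeld residuals and are "formally tested by performing the Grambsch-Therneau test". Two reporting rules follow. The HR, its 95% CI and its p-value appear whatever the check shows. The other measure is conditional: "If there is an indication of a non-proportional hazard rates, the restricted mean survival time (and its difference between arms" at t* = 5 years, with its confidence interval, is then reported, because the authors regard it as the more informative summary in that situation. Kaplan-Meier curves by arm are always plotted.

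The Secondary analysis section states that "OS and TFST are tested applying the same analysis as described for the primary endpoint", so the same condition applies to those endpoints.

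**The concern.** A screen run on the trial's own outcome data decides whether a pre-specified effect estimate is promised. If the screen is insensitive, a real but moderate waning or delay passes unnoticed, and the measure that the plan itself prefers for such cases need not be reported. If hazards are proportional, the measure appears only in those trials where the screen fires by chance. Either way, the reported set of estimates depends on a noisy signal. What is at stake is how the effect is described, and whether reporting is free of selection. The significance conclusion is not at stake.

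**Working it through.** **Inputs from the protocol article.** Sample size section, whole cohort: "Calculations were done assuming a two-sided alpha level of 5% and a log-rank test for comparison"; events were sought "to achieve a 90% power to detect a hazard ratio (HR) of 0.70 between the two treatment arms"; PFS is exponential and "the median PFS under standard care is 18 months"; the HR "would increase the median PFS in the treatment arm to 25.7 months". There are 330 events from 540 patients, uniform accrual over 3.5 years, and 10% dropout with no time scale. Randomization section: "Subjects will be assigned 1:1 to letrozole or placebo".

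**Assumptions.** Test level 5%; the departure patterns in the table; dropout of 10% over 5 years; no stratification by grade.

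**Step 1: the plan's own figure.** Schoenfeld: events = 4(1.96 + 1.2816)² / (ln 0.70)² = 42.03 / 0.1272 = 330.4. The stated 330 is reproduced (power 0.8997). The 540 patients are also reproduced to within 3%: 544 if dropout is 10% per year, 530 if a no-dropout sample size is divided by 0.90.

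**Step 2: closed form.** Compare an early log HR with a late one, from D1 and D2 events, with SE = √(4/D1 + 4/D2). The late/early HR ratio detected with a given power is exp[(1.96 + z) × SE].

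- Split 165/165: SE = √(8/165) = 0.220. Ratio for 50% power: exp(1.96 × 0.220) = 1.54; for 80%: exp(2.80 × 0.220) = 1.85; for 90%: 2.04.
- Split 110/220: SE = 0.234. Ratios 1.58, 1.92 and 2.13.

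This contrast knows where the effect changes. A trend test does not, so it should do somewhat worse.

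**Step 3: simulation.** 2,000 trials per pattern, 540 patients, control median 18 months, data cut at the 330th event, Grambsch-Therneau score test at 5%. Detection rate by time transform:

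| HR pattern (assumed) | Kaplan-Meier | identity | log |
|---|---|---|---|
| Proportional, 0.70 | 5% | 4% | 5% |
| 3-month delay, then 0.65 | 16% | 12% | 23% |
| 6-month delay, then 0.65 | 29% | 23% | 30% |
| 6-month delay, then 0.60 | 40% | 31% | 41% |
| 0.60, then 0.90 from month 18 | 30% | 30% | 20% |
| 0.60, then 1.0 from month 24 | 29% | 32% | 19% |
| 0.60, then 1.0 from month 18 | 44% | 43% | 29% |
| 0.55, 0.75 from month 12, 0.95 from month 24 | 44% | 44% | 33% |
| 12-month delay, then 0.50 | 73% | 71% | 58% |
| 0.50, then 1.0 from month 12 | 73% | 69% | 63% |
| 1.3 for 6 months, then 0.55 | 85% | 75% | 85% |
| 0.40, then 1.1 from month 12 | 96% | 94% | 92% |

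The first seven departures are moderate (ratio at most 0.95/0.55 = 1.73); the last four have a ratio of 2 or more.

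**Step 4: sensitivity.** Testing at 10% (Kaplan-Meier time) raises the moderate cases to 25-58%. Taking the largest of the three transforms at 5% gives 26-49%. A second simulation (1,500 trials per pattern, cut at month 60, loss of 10% per year, range over the three transforms) gave 19-34% for 0.60 then 1.0 at 24 months, 32-41% for a 6-month delay then 0.60, 60-74% for a 12-month delay then 0.50, and 54-61% for 0.55 then 1.0 at 12 months (ratio 1.82, between the two groups). With a month-60 cut, 10% dropout over 5 years and Kaplan-Meier time, moderate departures were detected in about 33-43% and strong ones in about 65-80% or more.

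**Step 5: does RMST change the significance conclusion?** Hardly. RMST at 48 months (a horizon chosen only for this check) had power within 3 points of the Cox test in every pattern, for example 0.86 for both with a 6-month delay then 0.60.

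**Step 6: is t* = 5 years estimable?** The Blinding procedures section puts the final PFS analysis at least 1.5 years after the last patient and at most 5 years 3 months in all. In the Step 3 simulation the 330th event falls at about 52-54 months, so essentially nobody is at risk at month 60. At month 63, only patients recruited in the first 3 months can reach it: 540 × 3/42 ≈ 39. Their mean PFS probability there is about (0.10 + 0.20)/2 = 0.15, so about 6 of 540 remain before dropout. The low-grade sample size section instead places this analysis about 5 years after the last patient. The two statements conflict.

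**The case against.** The strongest reply is that nothing inferential depends on the screen. Letting a pre-test choose the primary analysis would be harmful, and this plan avoids it: the HR, CI and p-value are fixed in advance, and RMST is a supplement. The Kaplan-Meier curves always appear, so a reader can see waning or delay whatever the test says. All of this stands, and it is why the point is minor.

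A reader might go further and infer three things that the document does not support.

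- *That the screen misses most plausible departures.* The document calls no departure plausible, and strong ones are detected more often than not.
- *That RMST is withheld.* The text does not forbid RMST in other cases; it only fails to require it.
- *That the indication could be called to suit the result.* Statisticians are blinded until the primary analysis has been performed. The test level, the time transform and the way plot and test combine may properly sit in the SAP, so their absence here is no defect.

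The calculation also covers the formal test only. The sensitivity of the visual check cannot be computed. If either signal suffices, the detection rates above are lower bounds on how often RMST would be triggered. No figures are available for OS or TFST.

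What survives is the stated rule itself: reporting of an effect estimate is tied to a noisy signal, with no benefit that would justify the condition.

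**Conclusion.** The point holds as a minor improvement to a stated rule. With about 330 events, a 5% Grambsch-Therneau test detects moderate departures in fewer than half of trials: 16-44% with Kaplan-Meier time, 12-44% over all three transforms. Strong departures are detected in roughly 65-95% (58% at the lowest, with log time). Under proportional hazards, RMST would follow a chance signal in about 5%. These figures rest on assumed departure patterns, an assumed test level, an assumed dropout time scale and an unstratified PFS simulation. The primary HR test and its power are unaffected. Removing the condition works only if the horizon is also made estimable, because t* = 5 years is not supported by the analysis timing in the Blinding procedures section.

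**What to change.** In the Primary analysis section, delete the condition. Suggested text: *The difference between arms in restricted mean survival time, with its 95% confidence interval, will be reported alongside the hazard ratio in all cases for PFS, OS and TFST, up to a horizon pre-specified for each endpoint and supported by follow-up. It is a supplementary estimate; the hazard ratio p-value remains the sole primary test. The Grambsch-Therneau test and residual plot are descriptive and do not decide what is reported.*

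Reconcile the two statements on when the final PFS analysis takes place, and set the horizon to match, before unblinding, in place of t* = 5 years. Deleting the condition without this step would require an estimate at a time when almost no one is at risk.

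The cost is a short wording change and one more result line per endpoint. Alpha, sample size and trial conduct do not change.
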